| Secondary Identifiers                                                 | ISRCTN.com Identifier: 14326006                                                                                                                                                                                                                                                           |
| Clinical Phase                                                        | III                                                                                                                                                                                                                                                                                       |
| Health Condition Studied                                              | Pre-Exposure Prophylaxis for COVID-19                                                                                                                                                                                                                                                     |
| Study Duration                                                        | Enrollment period: April 20, 2020 to July 30, 2021                                                                                                                                                                                                                                        |
|                                                                       | Study period: April 7, 2020 to January 30, 2022                                                                                                                                                                                                                                           |
| Primary Sponsor-Investigators                                         | [name] and [name]                                                                                                                                                                                                                                                         |
| Contact: Public Queries                                               | [name]
[name]
[name]
[name]
[contact] [name]                                                                                                                                          |

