| Duration of Treatment     | Three months hydroxychloroquine vs placebo (Day 1-90) followed by one additional month open-label hydroxychloroquine for all participants (Day 90-120)                                                                                                                                                                                                                                                                                                                                                                                                                                                                                                                                                                                                                                                                                                                                                                                                                                                                               |
| Outcome Measures          | 
Primary: Microbiologically confirmed COVID-19 (i.e. SARS-CoV-2 infection). This is a composite endpoint which includes any validated SARS-CoV-2 diagnostic assay including detection of viral RNA, and seroconversion
 
Secondary Outcome Measures:
 
 
a) Adverse events
 
b) Symptom duration of COVID-19
 
c) Days of hospitalization attributed to COVID-19
 
d) Respiratory failure requiring ventilator support attributed to COVID-19
 
e) Mortality attributed to COVID-19
 
f) Total days off work attributed to COVID-19
 
g) Seropositivity (reactive serology by day 120).
 
h) Short term psychological impact of exposure to COVID-19 at day 1, 60, 120 days.
 
                                                                                                                                                                                                                                 |

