## 2.4 Outcome measures

The **primary outcome is microbiologically confirmed COVID-19 (SARS-CoV-2 infection)**. This is a composite endpoint which includes any positive result from a validated SARS-CoV-2 diagnostic assay including detection of viral RNA, or seroconversion by day 104 (14 days after end of the randomization period).

The microbiologic outcome measures will be obtained from validated diagnostic assays performed on participant samples (viral detection samples or blood) collected at defined intervals over the course of the study (see Section 9.1 and Table 1, Schedule of Events). Symptomatic outcome measures, clinical outcomes (ex. hospitalization, need for supported ventilation), days unable to work etc. will be collected by self-report *via* weekly email survey (see Section 9.1 Table 9.1, Schedule of Events). In the case of death or other condition rendering the participant unable to communicate or complete the weekly email survey, the outcome will be obtained by contacting the designate identified by the participant at enrollment. If it is not possible to reach this person, the participant will be considered lost to follow up.

Per Public Health Agency of Canada, Public Health Ontario, and hospital guidelines, during this COVID-19 pandemic, all HCWs must report to occupational health and their departmental supervisors and self-isolate (i.e. they must not come to work) should they develop any signs or symptoms of COVID-19, at which time they will be prioritized for testing either in the emergency department or at occupational health (and less frequently at MOH testing centres), as per site institutional guidelines. Diagnostic testing will be prompted by symptoms and be conducted according to these routine channels. Results of these tests will be collected by the data collection measures in this study.

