### 3.6 Co-enrollment Guidelines

Co-enrollment into other investigational prevention studies will not be permitted at this time.

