## 4.0 WITHDRAWAL OF PARTICIPANTS

### 4.1 Withdrawal criteria

Participants may be withdrawn from the study if the Sponsor-Investigator terminates the trial (i.e. if new evidence emerges proving either futility or efficacy of the study drug or

potential safety concerns or if drug supply becomes an issue). Grade 3 or 4 adverse events or an SAE may warrant withdrawal from the study. If a new health condition emerges in a participant randomized to the HCQ arm that requires medications absolutely contraindicated by the protocol, then decisions regarding discontinuation of the study drug can be made at the discretion of the site investigator, but the participant should be retained in the study for ascertainment of the primary and secondary outcomes. Site investigators are encouraged to consult with the study pharmacist in such situations. Reasons for the discontinuation of study drug will be noted in the study database. If the participant discloses that they have been self-administering any other medication for the prevention of COVID-19, it will be noted in the database and the participant will be retained in the study for ascertainment of primary and secondary outcomes. If a participant withdraws from the medication, with consent, the participant will still be followed for primary and secondary outcomes.

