#### 8.2.3 SARS-CoV-2 Serology

Methods for serologic testing of COVID-19 are still in development worldwide at the time of writing, but are rapidly emerging. Participants will undergo venipuncture at baseline, and monthly until and including the 120 day visit and samples processed into plasma for frozen storage by [name] laboratory (co-PI). Frozen samples will be batch-tested in the laboratory of Co-I [name] at the conclusion of the study when methods are finalized.

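### Seroconversion on any validated assay meets the primary endpoint, with no antigen requirement and no rule for vaccination, so vaccine antibody could be scored as infection and dilute the hazard ratio

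*Protocol*

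**What the plan says.** Protocol Section 2.4 makes seroconversion sufficient by itself. The composite is met by "any positive result from a validated SARS-CoV-2 diagnostic assay including detection of viral RNA, or seroconversion by day 104". The synopsis agrees: "This is a composite endpoint which includes any validated SARS-CoV-2 diagnostic assay including detection of viral RNA, and seroconversion". Secondary outcome (g) in Section 2.4 is reactive serology by day 120, again without qualification.

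On the assay, Section 8.2.3 states: "Methods for serologic testing of COVID-19 are still in development worldwide at the time of writing". Plasma is taken at baseline and monthly, frozen, and batch-tested at the end of the study once methods are settled. No target antigen is named.

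On the calendar, the synopsis gives "Enrollment period: April 20, 2020 to July 30, 2021" and "Study period: April 7, 2020 to January 30, 2022".

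Vaccination appears nowhere. The nearest provisions are these:
- The exclusion criteria (3.3) are silent on it.
- Section 3.6 says: "Co-enrollment into other investigational prevention studies will not be permitted at this time". That covers other trials only.
- Section 4.1 says of a participant found to be "self-administering any other medication for the prevention of COVID-19, it will be noted in the database", and keeps that participant in follow-up for the outcomes.
- Section 6.6 has concomitant medications recorded at visits.
- Section 11.3.1 gives each participant either an infection date or a censoring date as uninfected, with no rule linked to vaccination.

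One section differs. Section 2.1 words the primary outcome as symptomatic COVID-19 with microbiological confirmation, within 104 days.

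**The concern.** The outcome is meant to be SARS-CoV-2 infection, but one of its sufficient criteria, as written, does not separate infection from vaccination. Take a participant who is seronegative on day 1, is vaccinated on day 40 and is reactive on day 60 on an assay that detects vaccine antibody. Under Section 2.4 that participant is an infection, and outcome (g) is met as well.

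Hydroxychloroquine has no reason to prevent such events. They would be expected at the same rate in both blinded arms, where they add noise to the comparison and move the hazard ratio towards 1. The cumulative incidence plot and the overall infection rates promised in Section 11.3.1 would also stop describing infection. A null result could then reflect an ineffective drug or diluted events, and the data as planned could not tell which: the weekly questionnaire (8.4, 9.5 and the notes to Table 1) lists test results, clinical outcomes, time off work and adherence, but not vaccination.

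**Working it through.** **Inputs from the protocol (11.2, 11.3.3).** Three-month control risk 10%; hazard ratio 0.588; one-sided 5%; 92 events; 988 participants, 1:1; follow-up 3 months plus 14 days; interim at 46 events with bounds Z > 2.67 (efficacy) and Z < −0.0142 (futility); final bound Z > 1.6549.

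**Assumption, not in the documents.** A share v of each arm seroconverts from vaccine within the 104 days, at a constant rate, on an assay that detects vaccine antibody.

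**Step 1: reproduce the plan.** Control hazard h0 = −ln(0.90)/3 = 0.0351 per month. Treated hazard 0.588 × 0.0351 = 0.0207. Follow-up T = 3 + 14/30.44 = 3.46 months. Expected events = 494 × [(1 − e^(−0.0351×3.46)) + (1 − e^(−0.0207×3.46))] = 494 × (0.1144 + 0.0690) ≈ 91, close to 92. Two-look power at 46 and 92 events with the stated bounds is 0.81 at HR 0.588 and 0.80 at 0.59. Type I error is 0.049 with the futility bound binding and 0.050 without. The stated design is sound on its own terms.

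**Step 2: add vaccine seroconversion equally to both arms.** Vaccine hazard hv = −ln(1 − v)/T. Observed HR = (0.588·h0 + hv)/(h0 + hv).

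For v = 5%: hv = 0.0513/3.46 = 0.0148; HR = (0.0207 + 0.0148)/(0.0351 + 0.0148) = 0.71.

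**Step 3: power under two readings of when events are counted.**

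(a) All events D to day 104 are counted after the study-end batch serology of 8.2.3, in a single final look: power = Φ(−ln(HR)·√D/2 − 1.6549). For v = 5%: D = 135.5, so 0.342 × 11.64/2 − 1.655 = 0.336 and power is 0.63.

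(b) The analysis is made at 92 events under the trigger in 11.3.3, using the two-look design with the diluted HR.

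| v | Observed HR | Events to day 104 | Of these, vaccine only | Power (a) | Power (b) |
|---|---|---|---|---|---|
| 0% | 0.588 | 91 | 0 | 0.81 | 0.81 |
| 5% | 0.71 | 135 | 47 (35%) | 0.63 | 0.49 |
| 10% | 0.78 | 180 | 94 (52%) | 0.51 | 0.32 |
| 30% | 0.90 | 360 | 283 (79%) | 0.27 | 0.13 |

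If an interim look at 46 events free of vaccine seroconversions precedes the final look in (a), power is about 0.64, 0.54 and 0.37 at v = 5%, 10% and 30%.

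**Step 4: type I error.** With a true HR of 1, adding the same hazard to both arms leaves the HR at 1. The false-positive rate is not raised.

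**The case against.** **The premise lies outside the documents.** The protocol does not say that a vaccine is available to these workers, how many would take it, or that the assay would react to it. This stands against any flat statement that vaccinees will be scored as infected, and it is why v is shown as a range that includes zero. It does not remove the point: the endpoint rule is on the page, and so are the enrolment dates.

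**The construct is infection, and the assay is still open.** The outcome is named as SARS-CoV-2 infection, and the serology method is to be finalised before the batch is tested. A laboratory manual or SAP could choose an antigen that avoids the problem, and the banked plasma would allow it. That makes the fix easy, but it does not amount to a rule. The protocol itself defines the endpoint, accepts any validated assay, and does not list vaccination among the data it collects weekly. Section 6.6 might capture vaccination as a concomitant medication, but nothing there changes how a seroconversion is scored.

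**Section 2.1 would limit the damage.** If the outcome is symptomatic disease, an asymptomatic vaccine seroconversion would not count. But Section 2.1 contradicts Section 2.4, the synopsis and Section 11.3.1, so it cannot be relied on.

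**Stronger readings that a reader might infer.** One is that false events would trip the 46- and 92-event triggers early. Section 8.2.3 tests serology at study end, so vaccine seroconversions would not accrue in real time, and the lower power figures (0.49, 0.32, 0.13) apply only if the analysis is nonetheless made at 92 events that include them. Another is that the trial could wrongly declare benefit; error that is equal in both arms does not do that. Section 4.1 is also weak support, since self-administered medication does not naturally describe vaccination.

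**Conclusion.** The point holds conditionally. Sections 2.4 and 8.2.3 allow vaccine antibody to count as a primary event, and no exclusion, censoring, co-enrolment or assay rule prevents it. Whether it does any harm depends on uptake during follow-up and on the antigen, and the documents give neither. The arithmetic also assumes a constant vaccine-seroconversion rate that is equal in both arms.

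Within those assumptions the loss is material even at low uptake. At 5%, about a third of events would be false and power would be about 0.63 with all events counted. At 10%, false events (94) would outnumber true ones (about 86). The direction is always towards no effect. The documents do not support saying that the trial's power is 0.49 or lower, or that its result is invalid; they support saying that the endpoint definition leaves this exposure open.

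**What to change.** Amend Sections 2.4 and 8.2.3. For anyone vaccinated on study, count a post-vaccination seroconversion only on an assay for an antigen that the vaccine received does not contain. Where no such assay applies, disregard serology after the first dose and rely on RNA detection, which Section 9.6 already samples every two weeks. Apply the same rule to secondary outcome (g), and carry the wording into the synopsis. Add vaccine received and date to the weekly questionnaire. In the same amendment, reconcile the symptomatic wording of Section 2.1 with Section 2.4.

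The cost is small: endpoint wording, one weekly question, and a constraint on an assay not yet chosen, applied to plasma already banked. The downside is somewhat lower serological sensitivity after vaccination, so some true infections detectable only by serology would be missed in both arms.

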## 1.0 INTRODUCTION, BACKGROUND, AND STUDY RATIONALE

### 1.1 Background

On March 11th, 2020, the World Health Organization (WHO) declared coronavirus disease (COVID-19) caused by severe acute respiratory virus coronavirus 2 (SARS-CoV-2) a pandemic. As of March 22, 2020 there have been over 267,013 confirmed cases and 11,201 deaths in 185 different countries or regions; it is quickly overwhelming health care systems worldwide to detrimental effect. Even with current moderate interventions imposed, estimates predict that 10-18% of the Canadian population will be infected with the virus by its peak in July. Health care workers (HCWs) remain a critical line of defence in the fight against this pandemic and maintaining their health is not only an important social responsibility of the government, but it is also of vital national interest to treat and control others infected with this virus or sick with other disease.

Estimates from China indicate that HCWs make up 3.8% of cases, while in Italy it is reported to be much higher – 8.3%. Early numbers from front-line workers in Italy suggested up to 20% of HCWs become infected with COVID-19, and these rates are approximately 3 times higher than the general population. When HCWs become sick, not only do they risk dying, but they also must take weeks away from work limiting the ability of the health care system to function. The fear associated with becoming ill also causes higher rates of missed work and higher rates of burnout, as seen with previous outbreaks. It is also now clear that asymptomatic transmission of COVID-19 not only occurs, but may even be the most important factor in spread of the virus. HCWs may therefore become vectors of viral spread to those who are the most vulnerable in other areas of the hospital. Preventing our HCWs from acquiring SARS-CoV-2 should therefore be of the utmost importance to our national interests.

### 1.2 Current Treatment Options

Repurposing drugs already known to be safe and tolerable in humans provides a major advantage in a pandemic where time is critical. Of candidate drugs, chloroquine (CQ) and its derivative hydroxychloroquine (HCQ), have shown some promise. Originally an anti-malarial medication, CQ exerts direct antiviral effects by inhibiting pH-dependent steps of the replication of several viruses, including coronaviruses. It also has immunomodulatory effects, suppressing the release of TNF $\alpha$  and IL-6, which are involved in the inflammatory complications of several viral diseases. *In vitro* data has shown that CQ potently blocks virus infection at low micromolar concentrations with a high selectivity index. CQ is also widely distributed throughout the body, including the lungs, after oral administration. An early clinical trial of more than 100 COVID-19 patients in China reported that CQ was superior to placebo in inhibiting pneumonia, improving lung

imaging, promoting viral seroconversion, and shortening the disease course, although data was not released. Based on those results experts in China recommended CQ 500mg twice daily for ten days in all patients with COVID-19. HCQ has also been shown to also have anti-SARS-CoV-2 activity *in vitro* and may actually be more potent. It has a better safety profile than CQ (during long term use), and allows a higher daily dose, with fewer concerns of drug-drug interactions. Preliminary clinical data also suggests that HCQ may lead to significantly faster viral clearance in COVID-19 patients as assessed by nasopharyngeal swab (70% vs. 12.5%,  $p=0.001$ ).

### 1.3 Potential Risks and Benefits to Human Participants

CQ and HCQ have a long history of safety when used for both malaria prophylaxis and in rheumatic disease. Very commonly occurring (>10%) adverse events include gastrointestinal (abdominal pain and nausea), with less commonly (1-10%) occurring events including blurring of vision, diarrhea, vomiting, anorexia, headache, emotional lability and skin rash. There is a low incidence of serious adverse events, most commonly occurring during chronic use (>5 years), with the main risk being macular retinopathy (<1%), which depends on the cumulative dose and permanent damage can be prevented with regular vision exams during treatment. Other rare events (<1%) include liver dysfunction, hypoglycemia and while HCQ can increase the QT interval, the frequency of this event is not known, but can be increased when used in conjunction with other drugs that prolong the QT interval. It has shown safe even in higher doses (up to 500mg/day of CQ base).

There may be no medical benefit to participants from participating in this trial as the efficacy of HCQ in the prevention of COVID-19 has yet to be shown. There may be non-medical benefits in contributing to research that might benefit others, and other emotional and social benefits, including empowerment that participants are taking another measure to potentially reduce their risk of infection of COVID-19.

### 1.4 Study Rationale

Currently, there are studies underway looking at treatment of COVID-19 with HCQ, as well as post-exposure prophylaxis (PEP); to our knowledge there are no studies of HCQ, or any other antiviral, for pre-exposure prophylaxis (PrEP). PrEP offers the ability to protect front-line HCWs from illness, decrease nosocomial spread of SARS-CoV-2, and prevent loss of work force due to illness. Rigorous testing of HCQ for this purpose is critical at this time. We therefore aim to conduct the first randomized placebo-controlled trial of HCQ to prevent COVID-19 infections in front line health care workers at high risk of SARS-CoV-2 exposure as we prepare for escalating rates of COVID-19 in Toronto, Canada.

## 2.0 STUDY OBJECTIVES AND DESIGN

### 2.1 Overall Study Design

The HEROS study is a double-blind, randomized placebo controlled trial of oral HCQ 400 mg taken once daily for three months as PrEP to prevent COVID-19 in front line health care workers at high risk for SARS-CoV-2 exposure.

The trial will recruit 988 HCW at high risk of COVID-19 exposure from five academic hospitals in downtown Toronto: University Health Network (UHN) [Toronto General Hospital (TGH) / Toronto Western Hospital (TWH)], St. Michael's Hospital (SMH), Sinai Health System (SHS), and Sunnybrook Health Sciences Centre (SHSC).

Within each site, participants will be randomly assigned to either the intervention arm with HCQ or the placebo arm using a fixed 1:1 allocation ratio produced by a computer-based random number generator using variable block sizes to ensure equal allocation to each group.

The rationale for conducting a randomized placebo-controlled trial is:

*first*, little is known to date regarding the effectiveness of HCQ against SARS-CoV-2 *in vivo*, yet *in vitro* studies signal plausibility of virucidal activity;

*second*, no data exist supporting the efficacy of any biomedical interventions in health care workers for preventing COVID-19.

Participants will be seen at baseline, and then undergo monthly follow-up at day 30, 60, and 90, 120. The primary outcome will be symptomatic COVID-19 (with microbiological confirmation of SARS-COV-2 infection) anytime within 104 days (= the 90 days of the randomization period plus 14 additional days to allow for viral incubation, delayed symptom onset and/or seroconversion).

At 90 days an open label extension wherein all participants are offered a one-month course of HCQ 400mg once daily for PrEP of COVID-19. The rationale for the open-label extension is that it will improve participant adherence to their allocation group during the randomization period. It will further allow additional evidence regarding adherence and safety. A period of one month will be offered as this is the amount of drug that is available for the study.

A Cox proportional hazards model, using a covariate for occupation (a proxy for risk of exposure) will be used to estimate the reduction in risk of the primary outcome associated with hydroxychloroquine use. Follow-up time for this outcome will extend from randomization to the first of: infection, or the end of the three-month randomized period (+ 14 days). One interim analysis will be carried out after half the expected number of infections (46/92) have occurred, with stopping for efficacy if the one-sided p-value for benefit is  $<0.0038$  or futility if the one-sided p-value for benefit is  $> 0.51$ . If efficacy is shown at this time, all participants will be offered open-label HCQ until the end of the full study period (Day 120). If the study is not stopped at the interim analysis and HCQ has not otherwise been shown effective at that time, all study participants will continue to receive blinded study drug until day 90, and then be offered one month of HCQ in an open-label extension (until day 120).

